### **Sample size**

The primary parameter is total energy expenditure. Dulloo *et al.* [13] report TEE values of  $9867 \pm 488$  kJ/day and  $9538 \pm 521$  kJ/day for green tea vs placebo [13]. With an  $\alpha$  of 0.05 and  $\beta$  of 0.10 (power=1- $\beta$ =0.90) the number of subjects needed is:

$$N = 21 \times (SD)^2 / (\text{mean1} - \text{mean2})^2 + 0.96$$

$$N = 21 \times (488)^2 / (9867 - 9538)^2 + 0.96$$

$$= 47 \text{ subjects needed}$$

Rounded up, 48 subjects will be included in the experiment which means that each group contains 12 subjects. When taking drop outs into account 193 persons need to be screened. For the Asians with the COMTH allele 17 people have to be screened to get 12 subjects, as the allele frequency is 70%. The allele frequency for the COMTL allele is 15%, which means that 80 people have to be screened. In Caucasians for either the COMTL allele as well as for the COMTH allele 48 people have to be screened, as the allele frequencies are 25%. In total this would mean that 193 subjects have to be screened in order to find 48 subjects. This is an obtainable number since habitual high coffee drinkers do not apply for entering the study as the poster and advertisements mention the inclusion criteria. Also, coffee consumption in Asian people is rather low compared with Caucasians.

An ANOVA repeated measures with post-hoc tests will be used to compare the effects of green tea on TEE and fat oxidation in subjects with different ethnicity and different COMT polymorphisms. A p-value <0.05 will be regarded as statistically significant.

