## **Objectives**

The objectives of this study are to determine the effect of the different COMT polymorphisms after ingestion of green tea on energy expenditure and fat oxidation in a respiration chamber when being fed in energy balance.

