### **Outcome parameters**

Endpoints of the study are:

Energy expenditure, substrate oxidation, hunger and satiety in subjects who differ in genetic polymorphism and /or in ethnicity. More detailed:

- Effect of green tea on total energy expenditure and substrate oxidation, measured in the respiration chamber
- Feelings of hunger and satiety measured with VAS
- Effect of the different polymorphisms in people with different ethnicities on the outcome of energy expenditure and substrate oxidation after supplementation of green tea

For further information see paragraphs above.

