### **Statistics**

The average of each group in each of the 2 conditions (green tea or placebo) is calculated for:

- Mm VAS at each time-point; the area under the curve (AUC) is calculated for hunger, satiety, fullness, thirst, desire to eat, time of desire of next meal. This is done with the trapezoid method.
- Conditions are compared using 4-factor ANOVA repeated measures with post-hoc tests to discriminate between groups, and will show possible differences in satiety and energy expenditure. To double-check the outcomes, paired sample T-tests will be performed as well.
- Comparison implies the clinical outcome parameters as mentioned in the paragraph above.
- All results will be visualized in graphs and tables for better understanding.

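### TEE is named as the primary parameter, but no single TEE test is: one p<0.05 rule over four green tea terms gives about an 18% chance of a false positive on TEE alone

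*Protocol*

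**What the plan says.** Protocol, Sample size, opens with "The primary parameter is total energy expenditure" and sizes the trial on a green tea versus placebo difference in TEE. It continues: "Rounded up, 48 subjects will be included in the experiment which means that each group contains 12 subjects". The same section applies a repeated-measures ANOVA with post-hoc tests to TEE and fat oxidation together, across ethnicity and COMT polymorphism, and closes with the only decision rule in the document: "A p-value <0.05 will be regarded as statistically significant".

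Other sections do not carry the ranking through:

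- Objectives states the aim as "to determine the effect of the different COMT polymorphisms after ingestion of green tea on energy expenditure and fat oxidation", with the two outcomes side by side.
- Outcome parameters lists as endpoints "Energy expenditure, substrate oxidation, hunger and satiety in subjects who differ in genetic polymorphism and /or in ethnicity", with no order among them.
- Statistics adds "Conditions are compared using 4-factor ANOVA repeated measures with post-hoc tests to discriminate between groups". It does not list the four factors or name a post-hoc method. It also plans paired t-tests as a double-check and six appetite AUCs.

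**The concern.** A primary variable is not yet a primary test. A repeated-measures ANOVA on TEE with condition, COMT and ethnicity produces several results about green tea: an overall effect, a difference by COMT, a difference by ethnicity, and a three-way term. Post-hoc group comparisons follow. The protocol points in two directions. The sample size rests on a plain green tea versus placebo difference, while the hypothesis at the end of the Introduction is that the high-activity COMT group responds more strongly, which is an interaction.

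Under the rule as written, any of these TEE results below 0.05 may be called significant, and any could be presented as the main finding. The same holds for fat oxidation, which shares the analysis sentence and the objective with TEE. At stake is how the trial's conclusion can be read: the 5% that governed the design would not describe the chance of a false-positive green tea or COMT finding.

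**Working it through.** **Step 1. The plan's own figure.** Inputs from Sample size: means 9867 and 9538 kJ/day (difference 329), SD 488, alpha 0.05, power 0.90.

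- 21 × 488² / 329² + 0.96 = 5,001,024 / 108,241 + 0.96 = 46.20 + 0.96 = 47.16. This is stated as 47 and rounded up to 48.
- 2 × (1.960 + 1.282)² = 21.0 reproduces the factor 21. A one-sided 0.05 would give 17.1.

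The design alpha is therefore two-sided 0.05, spent on one comparison of two means.

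**Step 2. The green tea terms.** The design has two conditions within subject and 2 COMT types × 2 ethnicities between subjects, in cells of 12. The terms involving condition are:

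1. condition;
2. condition × COMT;
3. condition × ethnicity;
4. condition × COMT × ethnicity.

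With equal cells these contrasts are orthogonal. They share one error term on 48 − 4 = 44 degrees of freedom.

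**Step 3. TEE alone, no effect of green tea in any group.** Chance of at least one p<0.05 among k independent tests = 1 − 0.95^k.

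- k = 1: 5%.
- k = 2 (condition, condition × COMT): 1 − 0.9025 = 9.75%.
- k = 4: 1 − 0.8145 = 18.5%, or 3.7 times 5%.

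The shared error term makes the tests slightly dependent. Two separate simulations of green tea minus placebo differences in four cells of 12 (20,000 runs each) gave 18.2% and 18.4% for k = 4. No secondary outcome and no assumed correlation enters this figure.

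**Step 4. TEE and fat oxidation.** The correlation between the two responses is not given in the protocol, so it is varied from 0 to 0.8.

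| Tests counted on the two outcomes | r = 0 | r = 0.5 | r = 0.8 |
|---|---|---|---|
| One term (condition × COMT) | 10.2% | 9.2% | 7.7% |
| Four green tea terms, first simulation | 33.2% | 31.1% | 26.9% |
| Four green tea terms, second simulation | 32.8% | 30.5% | 27.0% |

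Four terms on two outcomes therefore give about 31%, with a range of 27% to 33%.

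**Step 5. Sensitivity to the model.** Condition, COMT and ethnicity make three factors, while Statistics speaks of four and lists none. If the fourth were crossed with the other three and contributed one degree of freedom, there would be eight condition terms, and 1 − 0.95^8 = 34% on TEE alone. This is an assumption and is not relied on below.

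**The case against.** The strongest reply is that the protocol does have a hierarchy: TEE is named primary and the trial is sized on it. That stands. A reader might infer from the endpoint lists that no ranking exists, or that an appetite scale counts as much as TEE. The text does not support this. Those lists are silent on rank and do not cancel the statement in Sample size, and tests on other outcomes do not inflate the error of one pre-named TEE test. The difficulty is that no such test is named, so naming TEE leaves the 18% untouched.

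Other stronger readings also fail:

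- *That every test is unadjusted.* The protocol names no post-hoc method and excludes no adjustment, and a rule may sit in an analysis plan that was not available.
- *That the protocol breaks a promised 5% overall error.* It promises none. Its 0.05 is the alpha of the sample size and the general threshold.
- *That the paired t-tests are extra routes to success in each subgroup.* Statistics offers them only as a double-check. Run overall, they largely repeat the condition term.
- *That the false-positive chance is a half or more.* Such figures can be produced: 49% when unadjusted per-cell t-tests and pairwise comparisons are added, and 71% for four terms on nine outcomes (50% to 84% over the correlations tried). They rest on test families that the protocol does not specify.
- *That the Applications paragraph of the Summary builds claims on any positive test.* Its wording is tentative and tied to no particular test.

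It can also be said that multiplicity belongs in the analysis plan. That is fair for the post-hoc method. The choice of the deciding test is different: the protocol itself states the primary parameter, the analysis and the threshold, and together they leave several TEE results equally eligible.

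**Conclusion.** The point holds in a limited form. TEE is the named primary parameter, but no TEE contrast is singled out, and one blanket threshold covers all terms on TEE and fat oxidation. With no effect of green tea, the chance of at least one significant green tea term is about 18% on TEE alone and about 31% (27% to 33%) on TEE and fat oxidation, against a design alpha of 5%.

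The 18% assumes a condition × COMT × ethnicity model with equal cells, each term judged at 0.05. The 31% also assumes a correlation of 0.5 between the two outcomes. If the intended family were only the overall effect and the COMT interaction on TEE, the figure would be 9.75%. This should be corrected before the data are analysed. It does not mean that a single pre-named TEE test would exceed 5%.

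**What to change.** In Sample size, replace the general threshold sentence with a statement covering these points:

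1. The only confirmatory test is one named TEE contrast at two-sided 0.05. If the hypothesis in the Introduction is the target, that contrast is green tea × COMT.
2. Fat oxidation is secondary. Making its test conditional on a significant TEE contrast is an option, not a necessity.
3. The other ANOVA terms, the remaining substrate outcomes, the appetite AUCs and the paired t-tests are exploratory, reported with estimates and 95% confidence intervals.
4. Post-hoc group comparisons on TEE are Holm-adjusted. They are confirmatory only if the named contrast is significant, and otherwise descriptive.

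Objectives, Outcome parameters and Statistics should then use the same ranking, and Statistics should list the four factors.

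The change needs no extra subjects or measurements. A fat oxidation or subgroup result with a null TEE contrast becomes supportive only, and adjusted post-hoc tests lose some power. The stated 90% power was calculated for green tea versus placebo, so it does not carry over automatically if the interaction is the contrast chosen. The sponsor should say so when naming it.

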### **Methods and measurements**

#### **Screening**

During screening, which takes place in our lab at the university, height and body weight will be determined. A questionnaire on health, use of medication, smoking behaviour and alcohol, coffee and tea consumption will be completed as well as a questionnaire to characterize eating behaviour (TFEQ). The outcome of the questionnaire will give an indication whether a subject is in good health or not as they have to report their use of medicine, disease history of themselves and their family. Finally, healthy, non-smoking males and females aged 18-50 years and with a BMI ranging from 18 till 25 kg/m^2 that have either no food allergies, are non-restrained eaters, moderate alcohol consumers and low habitual coffee drinkers will

be included in this study. Gender has no effect on the outcome, therefore both men and women are included. The age range is determined in order to obtain a vast range of subjects without emphasis on effects of aging. Only adults will be included in the experiment and therefore it is chosen to take an age of 18 as a limit. Subjects older than 50 years are excluded as they might respond less to treatment than younger subjects (for instance menopausal women). The BMI range concerns normal subjects and has been chosen because we first want to test the hypothesis in this group. Testing the hypothesis in obese subjects will be the next step. Also, green tea can be used to prevent weight gain in the non-obese group. During the initial screening of the subjects 10 ml blood will be drawn to determine their polymorphism. The screening will last approximately 30 minutes and will not be compensated. Eventually the outcomes of the questionnaires and the analysis of the blood sample will give us an indication whether the subject is suitable for the study. Subjects do not have to prepare for this screening.

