## **Subjects**

Forty-eight healthy subjects (age 18-50 years and BMI 18-25 kg/m^2) from which 24 Caucasians and 24 Asians, from each ethnicity 12 with a COMTH allele and 12 with a COMTL allele, will be recruited. The subjects will be recruited via advertisements in the University building and in a local newspaper. Subjects have to be in good health, non-smokers, not using medication (except the use of contraceptive), at most moderate alcohol users (persons consuming less than 10 glasses/week) and also people who drink at most one cup of coffee per day. Dulloo et al. and Kovacs et al. showed that the effect of green tea administration was the highest in people who drunk less than 2 cups of coffee per day [13, 18]. During the initial screening 10 ml blood will be drawn from the subjects to determine the polymorphism. We choose to draw blood instead of taking a sample from the mucous membrane of the cheek as the latter results in 10-20% drop-outs during the analysis. This would mean that more subjects have to be screened or that subjects have to be screened more than once, in case the analyses fail which is more aggravating for the subjects than drawing 10 ml blood once. A questionnaire on health, use of medication, smoking behaviour, alcohol consumption and tea and coffee consumption will be completed. The Dutch translation of the Three Factor Eating Questionnaire (TFEQ) will be used to determine eating behaviour [19, 20]. Non-restrained eaters (<9 times factor 1), these are persons who are not consciously occupied with food and who are caloric restricted, will be selected.

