#### Protocol

Subjects will visit the university twice and during each visit they will stay in the respiration chamber for two days and nights (36hrs). During one of these visits subjects will test the treatment condition (green tea; 757 mg/capsule [84.5 mg EGCG + 2.1 mg caffeine], 3 capsules with each breakfast and dinner) and the other visit they will test the placebo condition (soy oil; 757 mg/capsule, 3 capsules with each breakfast and dinner). Subjects receive a glass of water in order to swallow the capsules more comfortably. Both visits are separated by a period of 4 weeks, which will prevent influences of the previous experiment and influences of differences in menstrual cycle phase on energy expenditure. The respiration chamber experiment starts in the evening of day 1 at 19:00h and ends at 07:00h on day 3.

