### **Safety and risks**

This study does not include any risk for the subjects. There are no risks for the subjects in using any of the meals because people with certain food allergies are excluded. Blood sampling during the screening is limited and without side effects, apart from its usual risks of minor bruising. Green tea is a natural product that has no side effects, catechins can only be toxic in extreme dosages that can not be reached by drinking tea. Caffeine is only lethal after approximately 10 grams, which equals more than 100 cups of coffee. The dosage used here for green tea is based on the study of Dulloo et al.[13] who conducted several trials with different dosages and found that the current dose was ideal. Berube-Parent et al. [32] who conducted a study with different dosages confirmed this, as they found no effect of increasing dosage. The deuterium and palmitic acid (a regular fatty acid) are also not dangerous as both are freely available in nature and food products. The body will process them comparable as when taken up via food products. They contain a marker that is involved in the processes in the body that we want to measure such as fat oxidation. The remaining will be excreted via urine and after measuring these they will be used to calculate the outcome. The stay in the respiration chamber is comfortable as it is designed as a hotel room and contains all devices to guarantee a pleasant stay. Subjects can leave the room whenever an emergency situation occurs. When two subjects participate at the same time there will not be a researcher present during the night, only in case of one subject the researcher will be present. Subjects are instructed on beforehand what to do in an emergency situation: where they have to walk to, which route they need to follow, which numbers to call and which alerts there are. Further security will be informed whenever there are subjects in the chambers.

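### The eligibility criteria for women aged 18-50 say nothing on pregnancy or breast-feeding while the protocol claims no risk, and the age limit of 50 only partly carries out the menopause reason given for it

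*Protocol*

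**What the plan says.** Eligibility is stated in three places: the Population paragraph of the Summary, the Subjects section, and Screening under Methods and measurements.

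- Screening admits "healthy, non-smoking males and females aged 18-50 years and with a BMI ranging from 18 till 25 kg/m 2", and adds food allergies, restrained eating, alcohol and coffee.
- Subjects sets the health and medication conditions: "Subjects have to be in good health, non-smokers, not using medication (except the use of contraceptive").
- On screening content: "A questionnaire on health, use of medication, smoking behaviour and alcohol, coffee and tea consumption will be completed". The health part is said to cover medicine use and personal and family disease history. The blood sample is taken for genotype.
- On the upper age limit: "Subjects older than 50 years are excluded as they might respond less to treatment than younger subjects (for instance menopausal women"). The same paragraph also says that the age range is meant to keep effects of ageing from dominating.
- On sex: "Gender has no effect on the outcome, therefore both men and women are included".
- The Protocol subsection separates the two visits by 4 weeks, partly to prevent "influences of differences in menstrual cycle phase on energy expenditure".
- Safety and risks opens with: "This study does not include any risk for the subjects".

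**The concern.** The main issue is who may be dosed. Women from 18 years qualify on age, BMI, health and habits alone, and contraceptive use is permitted but not required. They receive green tea extract capsules and a deuterium-labelled fatty acid. The safety section discusses meals, blood sampling, catechins, caffeine, the label and the chamber stay, but not pregnancy or breast-feeding. A blanket statement of no risk is thus made for a population that, on the written criteria, can include women whom the section does not assess. Because the visits are 4 weeks apart, a woman's status can also change between them.

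The second issue is consistency. The protocol expects that menopausal women may respond less and uses age as the filter, but the filter does not act on menopausal status itself. It also says that gender has no effect, while naming menopause as a possible modifier of response and menstrual phase as an influence on energy expenditure, its primary parameter. A weaker response in some women would dilute the effect. Menopausal status could also be spread unevenly over the four ethnicity-by-genotype cells, because subjects are not randomised to those cells.

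**Working it through.** **Text check.** The three eligibility statements and the screening content, set against each status:

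| Status | Exclusion criterion | Listed screening item | Mentioned elsewhere |
|---|---|---|---|
| Pregnancy | none | none named | no |
| Breast-feeding | none | none named | no |
| Menopause at 50 or younger | none | none named | only as an example behind the age limit |
| Menstrual phase | none | none named | as a reason for the 4-week gap |

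The BMI ceiling and the good-health requirement might keep out some of these women, for instance in late pregnancy, but only incidentally.

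**The plan's own figure.** From Sample size: means 9867 and 9538 kJ/day, SD 488, alpha 0.05, power 0.90.

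- Difference: 9867 − 9538 = 329 kJ/day.
- N = 21 × 488² / 329² + 0.96 = 47.16. The stated 47, rounded up to 48 (12 per cell), reproduces. This point disputes no figure.

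**Weaker response, upper bound.** Assume that one woman in a cell of 12 has no response at all.

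- Loss in the cell mean effect: 329/12 = 27 kJ/day. At half response it is about 14 kJ/day.
- Standard error of a cell mean difference, taking 488 as the SD of the within-subject difference (equivalent to a within-subject correlation of 0.5): 488/√12 = 141 kJ/day. Ratio: 27/141 ≈ 0.2.
- With a correlation of 0.9: SD = 488 × √(2 × 0.1) = 218, SE = 218/√12 = 63. Ratio: 27/63 ≈ 0.4.
- Three complete non-responders in one cell: 3 × 329/12 = 82 kJ/day, a quarter of the planned effect and still below one standard error of 141.

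**Dilution over the whole sample.** If a share f does not respond, the effect becomes 329(1 − f). The documents give no value for f, so these rows are illustrations. Power is for the protocol's own formula at n = 47.

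| f | Effect (kJ/day) | N by the protocol's formula | Power |
|---|---|---|---|
| 0 | 329 | 47.2 | 0.905 |
| 5% | 312.6 | 52.2 | 0.874 |
| 10% | 296.1 | 58.0 | 0.837 |
| 20% | 263.2 | 73.2 | 0.744 |

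**Drift between visits.** Assume that one woman's energy expenditure shifts by 100 to 300 kJ/day over the 4 weeks for reasons unrelated to the capsules. The mean difference then moves by 100/12 to 300/12 = 8 to 25 kJ/day in her cell, and by 100/48 to 300/48 = 2 to 6 kJ/day over all 48 subjects (0.6 to 1.9% of 329).

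**The case against.** The strongest reply has four parts.

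- *Menopause is only an example.* The age limit applies to men too and also serves to limit effects of ageing. An age cut-off need not be a perfect proxy to be reasonable. This stands. A reader might infer that menopause is the whole justification for the limit and that the limit therefore fails, but the text does not say so. What remains is that the stated example is only partly acted on.
- *Screening may well ask.* The health questionnaire is not reproduced and could hold items on pregnancy or menopause. This also stands: it cannot be asserted that screening does not ask. But no written criterion would act on the answer, and eligibility criteria belong in the protocol.
- *The gender sentence can be read narrowly.* If the outcome means the effect of green tea, a menstrual-phase influence on the level of energy expenditure can coexist with no sex difference in that effect, and the 4-week gap is meant to handle phase. That is fair for menstrual phase. It is less convincing for menopause, which the same paragraph ties to the response to treatment. The sentences need reconciling, but they are not a flat contradiction.
- *The crossover protects the estimate.* A constant difference in energy expenditure cancels within the subject. Only a different response or a drift between visits can matter, and both are small on the figures above.

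None of this answers the absence of a pregnancy or breast-feeding criterion beside an unqualified statement of no risk.

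**Conclusion.** The point holds as a gap in eligibility and safety wording. No criterion covers pregnancy or breast-feeding, and the no-risk statement is made without considering either. The mismatch between the age limit and its menopause example, and the tension around the gender sentence, are secondary matters of consistency.

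A reader might infer that such women would visibly bias the results. The documents do not support that. The 27 kJ/day per subject is an upper bound that assumes complete non-response, where the protocol says only that the response might be less. It is about 0.2 to 0.4 of a cell's standard error under the two correlations assumed. The sex split and age distribution are not given, so no count of affected women can be derived. The dilution and drift results rest on assumed inputs. The case for change is therefore mainly safety and coherence.

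**What to change.** 1. In Subjects and in Screening, add pregnancy and breast-feeding to the exclusion criteria. Ask about both at screening and again before visit 2.
2. In Safety and risks, limit the no-risk statement to the population actually admitted.
3. Record menopausal status at screening, and reconcile the age criterion with the reason given for it. Excluding all peri- and postmenopausal women is not needed to settle this point. It would be a trade-off against the broad range of subjects that the protocol seeks.
4. Reconcile the sentence that gender has no effect with the menopause sentence in the same paragraph and with the menstrual-phase sentence in the Protocol subsection.

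The cost is a few questionnaire items, a short repeat question before visit 2 and a few edited sentences. The sample size does not change.
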